### CMT diagnosis panel

3.5

#### CMT expert group

3.5.1

The CMT expert group contains 3 KMD members who satisfy at least 1 item of the following criteria:

1.A specialist with the certification of Korean Medicine Rehabilitation2.A certified lecturer or educational board member of the Korean Society of Chuna Manual Medicine for Spine and Nerves (KSCMMSN)3.An individual who completed the regular workshop of the KSCMMSN4.An individual with a published study regarding the spinal CMT diagnosis

#### CMT non-expert group

3.5.2

The CMT non-expert group contains 3 KMD members who perform CMT in clinical practice but do not satisfy the aforementioned criteria of the CMT expert group.

### CMT diagnosis methods in this study

3.6

#### Overview of CMT diagnosis

3.6.1

In CMT diagnoses, spinal alignment is assessed based on the relative 3D motion and alignment of the upper vertebral bodies to the lower vertebral bodies along 3 axes; vertical, anterior-posterior, and medial-lateral.^[5]^ With the neutral position as the base, malpositions related to the flexion and extension, right/left rotation, and right/left lateral bending are examined. Each malposition may appear on its own or in combination on a single lumbar level. In addition, for cases where axial alignment is disrupted or upper vertebral bodies show a slip in relation to the lower vertebral bodies, the diagnosis is *–lithesis*; anterolisthesis, retrolisthesis, or laterolisthesis, according to the direction of the slip (Fig. 2).

**Figure 2 F2:**
[figure not shown]
Classification system of spinal alignment diagnosis in Chuna manual therapy.

A more refined spinal alignment assessment is performed based on3 broad categories:

1.Any abnormality regarding CMT spinal alignment;2.The position of the lumbar level (multiple positions may be recorded) for the diagnosis of an abnormal CMT spinal alignment;3.The type of abnormality for the CMT lumbar level with a problem.

The panel diagnosis is to be based on answering questions under these 3 categories, while each is completely separate from the other, to prevent interference or interactions between investigator responses.

#### Palpation (manual) diagnosis

3.6.2

The CMT experts performing the manual diagnosis will follow the same SOP described below, which combines key contents from CMT textbooks and published articles for a manual diagnosis of spinal alignment.^[1,16]^

### Assessment of flexion/extension and rotation lateral bending malpositions

3.7

The subjects are guided to maintain the neutral position without flexion or extension of the spine, while the overall transverse and spinous processes are manually examined from the sacrum base to the lumbar spine to determine the positional characteristics across each segment.

The subjects are then guided to show the flexion, extension, left/right lateral bending, and left/right rotation motions, and as in 1), the transverse process of each motion is manually examined to assess the changes to the alignment at specific segments in contrast to the neutral position.

The spinal level with flexion or extension malposition is determined based on the reduced motion in comparison to the normal lumbar segments in the respective posture. Also, the spinal segments with left/right rotation or lateral bending malposition are determined based on reduced motion, in comparison to normal lumbar segments in the rotation or lateral bending of the opposite direction.

At the completion of all tests, the investigator records the defined type in the CRF.

#### Assessment of anterolisthesis, laterolisthesis, and retrolisthesis^[17]^

3.7.1

The subjects are guided to maintain the neutral position without flexion or extension of the spine.

The investigator stays behind the subject to monitor and assess the alignment of the spinous process of the lumbar spine and the symmetry of skin folds around the spine.

The investigator then manually examines the lumbar spine along the spinous process to assess any areas of dents or protrusions or bending towards a side away from the sagittal axis. If a dent is found upon the manual examination of the spinous process, the diagnosis is anterolisthesis. If a posterior protrusion is found, the diagnosis is retrolisthesis. If the spinous process is bent away from the central line of the spine despite the lack of abnormalities in 1), the diagnosis is laterolisthesis.

At the completion of all tests, the investigator records the defined type in the CRF.

#### X-ray test

3.7.2

The radiological diagnosis using X-ray images is performed by 2 groups; the CMT expert group (n = 3) and the CMT non-expert group (n = 3). The 2 groups receive anonymized lumbar X-ray AP and lateral view data in a file format, and, according to the same SOP used in prior CMT radiological diagnosis studies, the diagnosis is made based on the positions of vertebral bodies and the relative positions of surrounding structures.^[6]^ The spinal radiological examination results are based on the same categorization system and recorded in the same CRF documents used in manual diagnosis.

#### X-ray test using an AI program

3.7.3

An artificial intelligence (AI) program based on convolutional neural networks will be used in this study. CNNs are widely used in medical image analysis field due to their excellent performance. The AI program will be trained to automatically detect the vertebral feature points of the lumbar spine. The detailed program structure is described in reference 11. The AI program suggests the locations of 4 feature points per a vertebra. Figure 3 shows an example of the feature point locations suggested by the AI program. The performance of the AI program was reported with a success rate of 99.7% and a position error of 4.54 ± 3.00 pixels.^[9]^

**Figure 3 F3:**
[figure not shown]
Example of the feature point locations suggested by the AI program.

The CMT non-experts (n = 3) who perform the radiological diagnosis will once more be provided with the X-ray images, which will be identical to the previous ones, around a month after the initial diagnosis, together with an AI program. They will then use the AI program to perform a CMT radiological diagnosis based on the reference points suggested by the AI program, to assist with the detection of the positions of vertebral bodies in the lumbar spine. The results will all be recorded in the same CRF used in the manual and radiological diagnoses.

### Recruitment, randomization, blinding, and non-blinding

3.8

The subject recruitment ad will be posted on the hospital notice boards and websites of Wonkwang University Korean Medicine Hospital. All ads to be used in this study will first be approved by the IRB.

This study is an exploratory, cross-sectional, prospective observational study that does not involve randomization or a process related to blinding. However, to prevent evaluation bias, an independent investigator will perform the subject screening, collection of demographic data, and analysis of baseline health and medical history. All investigators in the CMT diagnosis will also be assigned an independent space to perform the evaluations, while any unnecessary talks or contact among different investigators or with subjects will be prevented during the evaluations, so that the investigators cannot acquire knowledge of the diagnosis results of other investigators. The investigators that perform the radiological diagnosis will solely use anonymized X-rays images, while appropriate measures will be applied to prevent the investigators from sharing the diagnosis data among themselves.

### Study outcomes

3.9

Within-group concordance between diagnosticians per diagnosis method

For the within- and between-group comparisons of the CMT diagnosis results, the following categories are set to evaluate the concordance. Through this, the concordance between diagnosticians can be compared for each diagnosis method, to determine the methods with higher concordance levels.

1.Concordance regarding spinal alignment abnormalities2.To evaluate concordance in relation to spinal alignment abnormality, an individual must show at least 1 single lumbar level abnormality.3.Concordance regarding the lumbar level with a spinal alignment abnormality4.To evaluate the concordance in relation to the lumbar level marked for spinal alignment abnormality.5.Concordance regarding the type of spinal alignment abnormality

To evaluate the concordance in relation to the type of spinal alignment abnormality.

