## Objectives

2

In this study, based on the CMT diagnosis of the lumbar spine, 4 diagnosis groups will be constructed;

1.CMT expert group (n = 3) for manual diagnosis;2.CMT expert group (n = 3) for radiological diagnosis;3.CMT non-expert group (n = 3) for X-ray radiological diagnosis;4.CMT non-expert group (n = 3) for AI-based X-ray radiological diagnosis.

The results will be collected for the specific diagnosis performed on the study subjects. Within- and between-group concordance levels will be subsequently compared to search for clinically effective CMT diagnosis methods. The potential use of the AI-based CMT diagnosis program will also be verified.

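### Section 3.9 compares within-group concordance across diagnosis methods without holding reader expertise fixed; three of the six group pairs change both, and palpation versus AI has no same-expertise contrast

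*Protocol article*

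**What the plan says.** The Objectives define four groups, each labelled by reader class and by method:

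- group 1: "CMT expert group (n = 3) for manual diagnosis"
- group 2: "CMT expert group (n = 3) for radiological diagnosis"
- group 3: "CMT non-expert group (n = 3) for X-ray radiological diagnosis"
- group 4: "CMT non-expert group (n = 3) for AI-based X-ray radiological diagnosis"

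The Objectives then give the purpose: "Within- and between-group concordance levels will be subsequently compared to search for clinically effective CMT diagnosis methods". Section 3.9 (Study outcomes) repeats it for within-group concordance: "the concordance between diagnosticians can be compared for each diagnosis method, to determine the methods with higher concordance levels". Section 3.10.2 assigns Fleiss' kappa to the three readers in each group.

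The methods sections agree with the four groups. In sections 3.2 and 3.6.2 only the experts palpate ("The CMT experts performing the manual diagnosis will follow the same SOP described below"). In section 3.7.2 both classes read unaided X-rays. In section 3.7.3 the AI program is used only by the non-experts, on the same images about a month after their first reading.

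Section 3.9.1 lists four between-group agreement comparisons. Its items 2 and 3, and the second advantage named in the Discussion, refer to a manual diagnosis by non-experts, which none of the four groups performs.

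**The concern.** There are three methods and two reader classes, but palpation is tied to experts and AI assistance to non-experts. Section 3.9 uses within-group kappas to find the more concordant methods and places no condition on which groups may be set against each other. Followed as written, it allows a difference between expert palpation and AI-assisted non-experts to be reported as a difference between methods, although the readers changed too.

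The study is exploratory, which lowers the stakes. But the Discussion expects the findings to help identify good diagnosis methods and to lead to further studies, so a confounded comparison would be carried forward.

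**Working it through.** The plan gives no figure to reproduce: section 3.4 sets 100 subjects by reference to earlier studies, without a formula. The check is a count of contrasts, then an estimability argument, then an illustration.

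**1. Cells filled** (Objectives; sections 3.2, 3.6.2, 3.7.2, 3.7.3)

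| | Palpation | X-ray | X-ray with AI |
|---|---|---|---|
| Experts | group 1 | group 2 | none |
| Non-experts | none | group 3 | group 4 |

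Two classes × three methods = 6 cells, of which 4 are filled.

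**2. Group pairs.** Four groups give 4 × 3 / 2 = 6 pairs.

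| Pair | Method differs | Expertise differs |
|---|---|---|
| 1 v 2 | yes | no |
| 3 v 4 | yes | no |
| 2 v 3 | no | yes |
| 1 v 3 | yes | yes |
| 1 v 4 | yes | yes |
| 2 v 4 | yes | yes |

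Two pairs change method only, one changes expertise only, and three change both. Method differs in 2 + 3 = 5 pairs, so 3 of those 5 are confounded with expertise. Counted by method instead, palpation v X-ray (experts) and X-ray v AI (non-experts) have a same-expertise contrast; palpation v AI does not.

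**3. Can palpation v AI be recovered?** Suppose expertise and method act additively on kappa. Let *a* be the value for expert palpation, *e* the shift for non-experts, *x* the shift for X-ray and *i* the shift for AI-assisted X-ray, both relative to palpation:

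- group 1 = a
- group 2 = a + x
- group 3 = a + e + x
- group 4 = a + e + i

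The direct difference, group 4 − group 1, equals e + i, so it carries the whole expertise effect. The chain (group 4 − group 3) + (group 2 − group 1) = (i − x) + x = i recovers the method effect. But the model has 4 parameters for 4 cells, so 4 − 4 = 0 residual degrees of freedom: the design cannot test the no-interaction assumption on which the chain rests.

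**4. Illustration of size (all inputs assumed, none from the document).** Take a binary finding marked in 50% of subjects, methods equally informative, and readers independent given the truth. Let each reader's latent score correlate ρ with the truth, so two readers correlate ρ². Then observed agreement is 1/2 + arcsin(ρ²)/π, chance agreement is 1/2, and kappa = (2/π) · arcsin(ρ²).

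- ρ = 0.8 (experts): (2/π) · arcsin(0.64) = 0.44
- ρ = 0.6 (non-experts): (2/π) · arcsin(0.36) = 0.23

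The apparent gap is 0.44 − 0.23 = 0.21, with no method effect at all. It would appear in all three confounded pairs, while 1 v 2 and 3 v 4 would show 0. With equal ρ in both classes the gap would vanish.

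**5. Does section 3.9.1 supply the restriction?** Item 1 is 1 v 2 and item 4 is 2 v 4. If the word manual in items 2 and 3 is a slip for radiological, these are 2 v 3 and 3 v 4. However, section 3.9.1 concerns agreement between two groups' diagnoses, whereas section 3.9 compares the internal agreement of one group with that of another. Two groups can each be internally consistent and still disagree with each other. The list therefore does not say which within-group kappas may be compared.

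**The case against.** The strongest reply is that the plan never announces a single ordering of the four groups. The Objectives label each group by expertise as well as method, and the list in section 3.9.1, read with the likely slip corrected, contains the three useful pairs and the expert benchmark but neither 1 v 3 nor 1 v 4. The Discussion puts the AI question as whether AI brings non-experts closer to experts, which is 3 v 4 with 2 v 4 as benchmark. Section 3.5.1 admits as expert anyone meeting one of four criteria, including completion of the society's regular workshop, so the expertise gap may be small.

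Much of this stands. A reader might infer that half of the method comparisons measure who read rather than how. The document does not support that: the three affected pairs differ in both respects, and the only pure reader contrast, 2 v 3, is not a method comparison. A reader might also infer that a four-group ranking is planned, or that the data say nothing about palpation versus AI. No section states the first, and the chain through X-ray answers the second, under its assumption. Nor is 2 v 4 an error when used as a benchmark.

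What the reply does not remove is the sentence in section 3.9. Its method comparison is unrestricted, and the list in section 3.9.1 concerns a different quantity and is itself partly inconsistent with the groups.

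**Conclusion.** The point holds in a limited form. As worded, section 3.9 allows method conclusions from three group pairs (1 v 3, 1 v 4, 2 v 4) in which expertise changes as well. Two of the three method questions have a same-expertise contrast; palpation versus AI has only an indirect one, resting on an assumption that the design cannot test.

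The count rests on the four groups in the Objectives. If non-experts do palpate, as section 3.9.1 and the Discussion suggest, palpation versus AI would gain a direct contrast among non-experts; hence the need to reconcile those places.

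Even the same-expertise contrasts are not perfectly clean. In 3 v 4 the AI reading always comes second on the same images, so order is mixed with AI. In 1 v 2 the document does not say whether the same three experts do both tasks, so expertise class is held fixed but not necessarily the readers.

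The size of any expertise effect is unknown. The gap of about 0.2 shows what is possible under assumed accuracies and is not an estimate for this study.

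**What to change.** In section 3.9, replace the open comparison of methods with named contrasts:

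- 1 v 2: palpation versus X-ray, in experts.
- 3 v 4: unaided versus AI-assisted X-ray, in non-experts, noting that AI is always the second reading.
- 2 v 3: expertise, on unaided X-ray.
- 2 v 4: benchmark only, asking whether AI-aided non-experts reach expert consistency.

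Estimate each as a difference in Fleiss' kappa with a confidence interval from resampling the 100 subjects, keeping all ratings of a subject together so that the pairing is preserved. State that 1 v 3 and 1 v 4 are not read as method effects and that the four groups are not ranked together. If the chained palpation-versus-AI estimate is shown, state its no-interaction assumption beside it.

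Reconcile items 2 and 3 of section 3.9.1 and the matching sentence in the Discussion with the Objectives and sections 3.2 and 3.6.2.

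The cost is wording in the protocol and analysis plan, with no new data. The price is that the study gives no direct manual-versus-AI conclusion.

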#### Monitoring of early termination, dropout, safety, and adverse events

3.9.2

As no specific intervention will be applied in this exploratory study for diagnostic purposes, no additional analysis will be carried out on early termination, dropout, safety, or adverse events.

### Statistical analysis

3.10

#### Demographic data and subject characteristics prior to treatment

3.10.1

The subject demographics and base characteristics will be analyzed using descriptive statistics. For continuous variables, the number of observed values, mean, standard deviation, median, and 25% and 75% percentiles will be used. For categorical variables, the frequency and percentage will be used.

#### Concordance analysis

3.10.2

To analyze the concordance levels for the results obtained by the 3 investigators in each group, the Fleiss’ Kappa evaluation will be used to determine the between-diagnostician concordance. If necessary, the Cohen's Kappa evaluation will be used to determine the between-investigator/group levels. For missing values, the Akaike information criterion will be applied.

### Data collection, access, management, and monitoring

3.11

All subject identification data will be anonymized using initials, and the data collected in this study will be recorded immediately in the relevant documents and the CRF. All subjects will maintain confidentiality of the results. All documents related to this study will be stored in a secure, isolated space according to the IRB regulations at Wonkwang University Korean Medicine Hospital. The data obtained in this study will be anonymized, and data access will be restricted to the investigators participating in the study and those included in the consent form, after approval from the principal investigator. All participating investigators will maintain confidentiality of the clinical outcomes.

Data management will be performed according to the clinical trial regulations at Wonkwang University Korean Medicine Hospital. An independent monitoring will also be performed according to hospital regulations at Wonkwang University Korean Medicine Hospital, to ensure the study is conducted in compliance with the clinical study protocol and the Korea Good Clinical Practice. During the monitoring period, the CRF will be reviewed based on a comparison with the evidential documents, to ensure the records are clear and complete.

### Ethics and Dissemination

3.12

#### Research ethics approval

3.12.1

This trial has received complete ethical approval from the Ethics Committee of Wonkwang University Korean Medicine Hospital (IRB 2021–8).

#### Protocol amendments

3.12.2

If protocol amendments are necessary, the relevant contents will be discussed with the principal investigator. If the clinical study protocol requires amendments, IRB approval will first be obtained. However, if in an emergency case occurs during the study period that demands the immediate treatment of the subject, the protocol may be altered, and the change will be reported to the IRB afterwards.

#### Consent

3.12.3

The recruited subjects will be given an adequate and detailed explanation of the study by an investigator who will not participate in the diagnostic process. If a subject has a question regarding the study flow, a request for adequate explanation can be made to the investigators participating in the study. The subjects who agree to participation in the study will subsequently submit a signed consent form.

#### Confidentially

3.12.4

All subject identification data will be anonymized using initials or symbols. All contents related to the results of the clinical study will be privately maintained by each diagnostician, who will also store the signed consent from the subjects and create a list of data that contains the subject's name, identity, and registration number for future reference.

#### Rescue therapy and post-trial care

3.12.6

This study will be conducted as an exploratory, cross-sectional, prospective observational study to collect the diagnostic results. As it does not involve clinical interventions, no additional regulations will be developed regarding post-trial care. However, if an emergency occurs during data collection, appropriate measures will be taken in accordance with the emergency protocols at Wonkwang University Korean Medicine Hospital and in compliance with the Korea Good Clinical Practice guidelines and the revised version of the Declaration of Helsinki, to ensure ethical and scientific considerations.

#### Dissemination policy

3.12.7

The findings in this study will be disseminated through peer-review journals and/or conference presentations.

## Discussion

4

The purpose of this clinical study is to compare and collect the evidence of the diagnostic concordance between diagnosticians and the diagnostics most widely used and well-known in CMT. The study has the following advantages: First, among the studies published so far regarding CMT diagnosis, this study proposes a design based on the largest number of cases and diagnosticians. Previous studies either had a very small number of cases or relied solely on a single diagnostician to pose a difficulty in defining sufficient rational evidence of the diagnosis outcomes.^[13]^ Thus, it is anticipated that the present study will provide the basic data for establishing a higher level of evidence in the CMT diagnostic field.

Second, most previous studies on manual diagnoses obtained the diagnoses based on the personal experience of the diagnostician, without an established SOP and compared the outcomes. On the contrary, the diagnosis in this study is performed according to an SOP that was produced using the contents of regular educational courses conducted by all Korean Medicine colleges in South Korea and by the KSCMMSN. The type of diagnoses are also specified based on the respective spinal abnormality, lumbar level with abnormality, and type of abnormality, to allow an in-depth analysis of the items with a high level of diagnostic concordance and those with a low level of concordance. Through this process, the rational diagnostic capabilities of current regular educational courses can be verified. The study will also provide basic data for developing further diagnostics or educational methods for items with a high error rate. In addition, comparing the manual diagnosis results between the CMT expert and non-expert groups is likely to induce additional discussions on methods for improving diagnoses by non-expert groups.

Lastly, the significance of this study lies in its being the first clinical study to apply an AI program in CMT as well as in the field of manual medicine, to the best of our knowledge. For CMT radiological diagnoses assisted by an AI program, the potential use of AI-based CMT diagnosis programs in clinical practice can be tested by determining whether the methodology results in an improvement in diagnostic concordance by CMT non-experts compared to CMT experts.

While this is an exploratory study, its findings are anticipated to provide basic data for identifying CMT diagnosis methods with high levels of rationality and evidence and in the development of CMT AI programs. Furthermore, the study results will lead to additional clinical studies that use CMT diagnosis methods and AI programs with reinforced evidence.
